### Safety evaluation

During the treatment, adverse events (AE) will be monitored through patient reports and assessments by medical workers. Adverse events include intolerance to electroacupuncture, fainting from needling, needle retention, subcutaneous bruising, local infection, etc. If a patient is intolerant to electroacupuncture, the trial can be suspended, and they may withdraw from the study. In the case of fainting, needle retention, subcutaneous bruising, follow the general procedures for the cases mentioned above, and promptly document the actions taken. Bleeding upon needle removal is common in acupuncture, and it has been proven to have therapeutic effects. Mild bleeding during acupuncture is addressed by applying pressure with a dry cotton for quick haemostasis and is not considered an adverse event (AE). For infections, consultation with a dermatologist is recommended. If serious adverse events (SAE) occur that result in disability, pose a threat to life, or lead to death, the trial should be immediately halted. Emergency measures should be taken to actively rescue the patient, stabilize vital signs, and promptly report the incident to the responsible authorities.

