#### Discontinuation criteria

Participants request to leave the study;Severe complications or infection occur post-surgery, in which the patient is to be transferred to another department for further specialized treatment;Severe allergy or adverse events occur during the interventional period.

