**Fig. 1 Fig1:**
[figure not shown]
CONSORT flow diagram of study design

After the intervention period, the participants will receive postoperative care according to the guidelines of the Gastrointestinal Surgery department until they are discharged from hospital. Participants in the CG group will be invited to receive 5 acupuncture treatments free of charge on voluntary basis as post-trial care.

Follow-ups will be done on the first month and third month after the surgery.

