#### Interventional group – electroacupuncture group (EG)

Participants in the EG will receive electroacupuncture therapy every day for 5 days consecutively, from the first day post-surgery onwards, each session lasts 20 min. Single-use acupuncture needles (diameter 0.30 mm, length 40 mm, China Suzhou Medical Appliance Company 20162200970, Hwato) will be inserted on acupoints Neiguan(PC6), Gongsun(SP4) bilaterally, 4 acupoints in total (Table 1), after the sites of insertion are disinfected. Acupuncturists shall then perform gentle manipulations on all acupoints until muscle twitch responses are sought from participants. Next, paired alligator clips of the electroacupuncture apparatus (China Suzhou Medical Appliance Company 20172200710, Hwato) are attached at bilateral acupoints (PC6 to SP4, lengthwise), with a continuous wave of 10 Hz and a current intensity of 0.5 mA to 2 mA, depending on the patient’s tolerance level. The location of acupoints is referenced from “Nomenclature and Location of Acupuncture Points” (GB/T 12346 − 2021).

**Table 1 Tab1:** Locations of Neiguan (PC 6) and Gongsun (SP 4)

Acupoints	Locations	Depth of insertion
Neiguan (PC 6)	On the palmar aspect of the forearm, 2 cun above the transverse crease of the wrist, between the tendons of m. palmaris longus and m. flexor carpi radialis.	15–30 mm, vertically
Gongsun (SP4)	On the medial aspect of the foot, in the depression distal and inferior to the base of the first metatarsal bone	15–25 mm, vertically

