### Data collection

For the SAS, FIRST, TCM rating scale of Gastrointestinal symptoms, GSRS, safety evaluation of electroacupuncture and evaluation of the resistance towards electroacupuncture, the questionnaires will be done in Case Report Form (CRF). Three scale questionnaires shall be filled by the patients themselves or under assistance of appointed data collectors according to the participant timeline (Table 2). Participants will complete the first questionnaire before the first treatment, while the second and the third questionnaire shall be collected after the treatment on the 3rd and 5th day respectively. Data collection will be done by data collection team instead of the acupuncturists to ensure neutrality of the results.

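### The stated adverse event window ends with the fifth session, so delayed non-serious events have no stated collection route although contact runs to three months

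*Protocol article*

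**What the plan says.** All references are to the protocol article.

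- **Window.** Safety evaluation states: "During the treatment, adverse events (AE) will be monitored through patient reports and assessments by medical workers". No other period for adverse event monitoring is given.
- **Events named.** The same section continues: "Adverse events include intolerance to electroacupuncture, fainting from needling, needle retention, subcutaneous bruising, local infection, etc". The list is open, but every example is a needling event.
- **Length of treatment.** The electroacupuncture group receives "electroacupuncture therapy every day for 5 days consecutively, from the first day post-surgery onwards, each session lasts 20 min". The placebo group is needled on the same schedule.
- **Later contact.** After the intervention, participants remain under the surgical department's care until discharge, and "Follow-ups will be done on the first month and third month after the surgery" (Procedure, text after Fig. 1). The Follow-up section gives the content: the QoL-C30 before discharge and at both later contacts, or a telephone call about the patient's status if no visit is needed.
- **Serious events.** Blinding counts serious surgical complications among the serious adverse events that lead to unblinding. Safety evaluation requires the trial to be halted and the event reported when a serious adverse event occurs. Neither provision carries a time limit.
- **Post-trial acupuncture.** Procedure offers control participants five free acupuncture sessions after the intervention period.

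**The concern.** The window does not fit the harms that the section itself lists. A faint or a retained needle is seen at the session. A local infection, and sometimes a bruise, may show only later. For the last session, any such event falls outside the stated window unless it appears before that treatment day is over.

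Non-serious surgical complications are in a similar position. They can arise after day 5 in patients recovering from laparoscopic cancer surgery, and the article does not say how they are recorded.

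What is at stake is the safety description, not the efficacy result. A site that followed the stated window could produce a reassuring table without having asked about delayed events at contacts it was making anyway. Any difference between arms in such events would not be captured systematically.

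**Working it through.** No formula tests this point. The check sets the sections side by side.

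**1. When the window closes.** Monitoring runs during treatment (Safety evaluation). Treatment is one session a day for 5 days from the first day after surgery (Interventions, both groups). The stated window is therefore postoperative days 1 to 5, and its last day is the day of the last session.

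**2. How the window compares with planned contact.** Taking a month as 30 days (an assumption):

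- to the 1-month contact: 5 / 30 = 0.167, about 17%
- to the 3-month contact: 5 / 90 = 0.056, about 6%

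**3. What the later contacts collect.**

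| Contact | Content named | Adverse event item named |
|---|---|---|
| Ward stay after session 5 | routine postoperative care | none |
| Before discharge | QoL-C30 | none |
| 1 month | QoL-C30, or status by telephone | none |
| 3 months | QoL-C30, or status by telephone | none |

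**4. Who would notice a later event.** Blinding asks the acupuncturists to record adverse events, but their stated task is to deliver the sessions, and no trial session follows the fifth. Safety evaluation adds patient reports and assessment by medical staff, again within the treatment period.

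**5. Which events are left without a route.**

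| Event first seen after day 5 | Stated route |
|---|---|
| Serious adverse event, including a serious surgical complication | yes: Blinding and Safety evaluation, no time limit |
| Non-serious needle-site infection or bruise | none stated |
| Non-serious surgical complication | none stated |

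Safety evaluation describes serious events as those that cause disability, threaten life or lead to death. An ordinary needle-site infection does not meet that description, so the provisions for serious events do not pick it up.

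**6. A complication for any extension.** The free acupuncture after the intervention period is offered to the control group alone. A late needle-site event in a control participant could come from that needling, so extended collection has to tell the two sources apart.

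**The case against.** The strongest case on the other side is that this is a condensed article. The items on follow-up forms and the safety follow-up of discontinued participants often sit in the full protocol or the case report form. The status call is open-ended and could bring harms to light. The primary outcome is first flatus time, and no safety comparison is stated as an objective.

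Part of this stands. Silence alone would not be a finding, and the primary result is not touched. But the article does more than stay silent. It states a monitoring window and it states the content of the later contacts, and the two do not meet.

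Four stronger readings are tempting, and the document does not support them.

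- **That monitoring is confined to treatment and later recording is excluded.** The section gives a period. It does not forbid recording outside it.
- **That all later surgical complications go uncounted.** Serious ones are covered without a time limit, and Discontinuation criteria also names severe postoperative complications or infection without a window. Those provisions say what to do once an event is known; they do not say how later events are sought.
- **That the last safety form falls on the day of the last session.** Data collection lists the safety evaluation with the scales and says "the second and the third questionnaire shall be collected after the treatment on the 3rd and 5th day respectively". That schedule belongs to a passage about the scales: "Three scale questionnaires shall be filled by the patients themselves or under assistance of appointed data collectors according to the participant timeline (Table 2". Table 2 is not visible here and may schedule the safety form differently.
- **That the criterion "Severe allergy or adverse events occur during the interventional period" also closes the safety window on day 5.** It is a rule for stopping treatment, which can only happen while treatment is running. It says nothing about when adverse events are collected.

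Counting the insertions made late in the treatment period would not measure the harm either. It would need an infection latency that the document does not give, and full adherence, although the sample size allows for 15% dropout.

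**Conclusion.** The point holds in a limited form. The stated window covers 5 days of a follow-up of about 90. Within the events it names, local infection and bruising can become apparent after it closes. Delayed non-serious needling events and non-serious surgical complications have no stated collection route after day 5, so they would not be captured systematically in either arm.

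How many events would be missed cannot be estimated, because the document gives neither a rate nor a time to onset. The conclusion rests on reading the window in Safety evaluation as written, and on the follow-up content being what the Follow-up section names. Confidence is moderate: Table 2 and the full protocol are not visible and could narrow the gap. The correction is worth making because it is cheap and the safety report depends on it. It does not affect the primary analysis.

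**What to change.** 1. In Safety evaluation, state that adverse events are collected from the first session through discharge, in both arms, including participants who discontinue.
2. Add a short check to the existing pre-discharge, 1-month and 3-month contacts, covering needle-site infection, bruising, surgical complications and readmission.
3. Record whether and when a control participant has taken the post-trial acupuncture. Report needle-site events before and after it separately.
4. Report events up to day 5 and after day 5 separately.
5. Reconcile the revised window with Procedure, Follow-up, the serious-event provision in Blinding, and Table 2.

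The cost is a few sentences in the protocol and a few form items at contacts already planned, with no new visits. More background surgical events will be recorded in both arms; reporting by arm and by period keeps them interpretable.

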#### Control group – placebo group (PG)

Participants in the PG will similarly receive electroacupuncture therapy every day for 5 days consecutively, from the first day post-surgery onwards, each session lasts 20 min. However, needles are applied on non-acupoints (1 cm apart from the acupoints of EG), with no needle manipulations performed(Fig. 2). To ensure the implementation of blinding, electrodes are attached, with a continuous wave of 10 Hz, but a lower current intensity of 0.1 mA.

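### Mild needle-site bleeding, which the protocol calls common, is excluded from the adverse events while bruising is counted, so any needle-related adverse event rate is incomplete by an unknown amount

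*Protocol article*

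**What the plan says.** The Safety evaluation section of the protocol article gives an open-ended list of what counts: "Adverse events include intolerance to electroacupuncture, fainting from needling, needle retention, subcutaneous bruising, local infection, etc". It then says of bleeding: "Bleeding upon needle removal is common in acupuncture, and it has been proven to have therapeutic effects". The next sentence sets the rule: "Mild bleeding during acupuncture is addressed by applying pressure with a dry cotton for quick haemostasis and is not considered an adverse event (AE". The rule is the same for both arms and covers only bleeding judged mild. No threshold for mild is given, and no bleeding rate.

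The arms differ at the needle. In the electroacupuncture group (EG), "Acupuncturists shall then perform gentle manipulations on all acupoints until muscle twitch responses are sought from participants", followed by a current of 0.5 to 2 mA. In the placebo group (PG), "needles are applied on non-acupoints (1 cm apart from the acupoints of EG), with no needle manipulations performed", and the current is 0.1 mA. Both groups are needled daily for five days.

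The Blinding section says that the acupuncturists cannot be blinded and asks them to record adverse events. The Safety evaluation section adds that events are picked up through patient reports and assessment by medical workers. The Data collection section mentions a safety evaluation of electroacupuncture on the case report form (CRF), but the form is not shown.

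**The concern.** This is a written exclusion, not a detail left to a fuller document. It treats two minor needle-site events differently: bruising enters the adverse event count and mild external bleeding does not. Frequency is a poor reason to exclude an event, because a common event is one that a trial of 104 people has some chance of estimating. A claimed benefit is no better a reason, because whether an event is harmless or helpful is a question for the data.

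At stake is how complete the safety description is. Participants are 40 to 89 years old and are needled from the first day after cancer surgery, so a reader will want to know how often needle sites bled, and in which arm. The rule takes mild bleeding out of the adverse event comparison between two arms that are needled differently. It also leaves the line between mild and countable undefined, in a trial where some of the people recording events know the allocation.

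**Working it through.** The plan states no adverse event or bleeding rate, so there is no figure to reproduce. The check has two parts.

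**1. The rule set against its neighbours**

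| Event | Status in the Safety evaluation section | Ground offered |
|---|---|---|
| Subcutaneous bruising | Adverse event; actions taken are documented | none needed |
| Local infection | Adverse event | none needed |
| Mild needle-site bleeding | Not an adverse event | Called common and therapeutic in the sentence before; described as quickly controlled |
| Bleeding beyond mild | Not excluded by the rule | – |

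By definition, a participant whose only event is a mild bleed counts as having no adverse event. If there is at least one such participant, the reported proportion is below a full count. That conclusion needs no assumed rate.

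**2. How large the omission could be (illustration only)**

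Inputs from the protocol article:
- Needle sites per EG session: 4 ("Neiguan(PC6), Gongsun(SP4) bilaterally, 4 acupoints in total").
- Sessions: 5 ("Participants in the EG will receive electroacupuncture therapy every day for 5 days consecutively").
- Participants per arm: 52 (Sample size section).

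Inputs assumed here, because the documents give none: a bleed probability p of 1% to 5% per insertion, independence between insertions, all bleeds mild, and all sessions completed.

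- Insertions per EG participant: 4 × 5 = 20. Insertions in EG: 52 × 20 = 1,040.
- Expected bleeds in EG: 1,040 × 0.01 = 10.4, up to 1,040 × 0.05 = 52.
- Share of participants with at least one bleed, 1 − (1 − p)^20:
  - p = 1%: 1 − 0.99^20 = 0.182, about 9.5 of 52.
  - p = 5%: 1 − 0.95^20 = 0.642, about 33.4 of 52.
- Effect on an any-adverse-event proportion, if a further assumed 5% of participants have some other, independent event: the rule would give 5%, whereas a full count would give 1 − 0.95 × (1 − 0.182) = 22.3% at p = 1% and 1 − 0.95 × (1 − 0.642) = 66% at p = 5%.

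Sensitivity to the assumptions:
- *Clustering.* If bleeding were confined to people who bleed at every insertion, the share affected would fall to p itself, 1% to 5%. The independence figures are therefore the high end for a given p.
- *Dropout.* With the planned 15% dropout, 52 × 0.85 is about 44 completers. If dropouts contributed nothing, there would be 44 × 20 = 880 insertions and 8.8 to 44 bleeds.

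**Difference between arms.** This takes 20 insertions in PG as well, which is an assumption because the text does not state the number of PG needles. The share with at least one bleed is 18.2% at 1% per insertion, 33.2% at 2% and 45.6% at 3%.
- Equal rates: difference 0.
- EG 2%, PG 1%: 33.2% − 18.2% = +15.0 points.
- EG 2%, PG 3%: 33.2% − 45.6% = −12.4 points.

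The documents do not rule out any of these, so neither the size nor the sign of a between-arm difference can be derived.

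**The case against.** The strongest reply is that this is an openly declared convention. Mild bleeding on needle removal is an expected, quickly controlled effect of the procedure. The rule is prespecified, is the same in both arms and leaves bleeding beyond mild countable. The stated aims concern efficacy, so little turns on a tally of trivial bleeds. Much of this stands, and it is why the point is minor. It does not explain why bruising is counted and bleeding is not.

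Several stronger readings are tempting, and the documents do not support them:

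- *The omission flatters EG in particular.* The difference in manipulation and current is documented, but nothing links either to bleeding. The manipulation is described as gentle, both arms are needled, and the PG insertion depth is not stated.
- *Bleeding is excluded because it is thought therapeutic.* The therapeutic remark stands directly before the exclusion, but no causal word joins them. The text also calls bleeding common and quickly stopped, which may be the real reason.
- *The unblinded acupuncturist decides what is mild.* The acupuncturists record adverse events, but nothing says who grades a bleed, and patients and other medical workers also report.
- *The trial cannot report bleeding.* An event that is not an adverse event may still be recorded. The CRF safety form is not shown and might capture it.
- *18% to 64% of participants will bleed unreported.* That range rests on an assumed rate and on independence. It shows that the unknown rate matters, and does not measure an understatement.

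**Conclusion.** The point holds in a limited form. The protocol article counts bruising but excludes mild bleeding, an event that it calls common, and neither frequency nor a claimed benefit justifies the exclusion. Any needle-related adverse event rate reported under this rule omits participants whose only event is a mild bleed. The direction of that effect on each arm's rate follows from the definition; its size does not follow from anything in the documents. Whether it differs by arm is unknown, but the trial should be able to check, given the documented differences in needling and the unblinded recorders. The primary outcome, the other efficacy results, alpha and power are untouched. This is a minor, cheap improvement and does not threaten the trial's main conclusion.

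**What to change.** In the Safety evaluation section, remove the statement that mild bleeding is not an adverse event. Replace it with a recording rule: every needle-site bleed, in both arms, is entered on the CRF at each session as an expected event, with a grade defined in advance (for example by how long it took to stop). Report the number of participants and the number of bleeds by arm, next to bruising. Listing it as an expected event keeps it apart from unexpected harms, and a defined grade removes the reliance on an undefined mild. Bedside handling stays as written.

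If the CRF safety form already captures bleeding, only the exclusion sentence and the reporting statement need to change. If recruitment has begun, make the change by amendment in both arms at once and give the sessions covered as the denominator, since bleeds not noted at the time cannot be reliably recovered.

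The cost is one sentence, one CRF item per session and a reported event rate that looks less favourable.

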### Ethics and dissemination

This study protocol and informed consent materials have been approved by the Ethics Committee of Shanghai Seventh People’s Hospital affiliated to Shanghai University of Traditional Chinese Medicine; Committee approval number: 2023-7th-HIRB-078. Informed consent shall be obtained from each participant before they take part in the study. There will be prior contact with participants by the nurses or researchers before the enrolment phase, where all information about the study and the objectives, its risks and benefits will be presented. They are free to abandon the study at any time without the obligation of giving any explanation.

### Protocol amendments

If any amendments to the study are required, they shall be collaboratively agreed upon by the research team and subject to approval by the sponsor in advance. Subsequently, the research department of the Shanghai Seventh People’s Hospital will notify the China Medical Research Registration and Filing Information System of these approved changes. All modifications to the protocol will be documented, and the protocol will be accordingly updated in the clinical trial registry.

### Confidentiality

Research data will be securely stored using a study identification code assigned to each participant. The identification code list will be accessible to the research team only during the study and will be documented and safeguarded by the principal investigator upon completion of the study, in accordance with research guidelines. Patient identification details will not be disclosed in any publications.

The biological samples collected in this study will be managed by the Laboratory Department of Shanghai Seventh People’s Hospital, an entity accredited by ISO 15189. These samples will serve solely as efficacy indicators and will not be utilized for genetic or molecular analysis.

Access to the datasets generated during the current study will be available upon reasonable request through the corresponding author.

